## Abstract

Background: The increase of the aging population is a challenge to society, as age is related to dependence. Injuries such as hip fractures cause morbidity, loss of independent life, and mortality. The purpose of this protocol is to describe a randomized control trial, with three intervention arms, aiming at investigating if there are any differences in outcomes after hip fracture between different rehabilitation interventions including (1) High-Intensity Functional Exercise (HIFE), (2) HIFE with the addition of continuous measures of movement and body positions with a wearable device, or (3) standard rehabilitation. A secondary aim is to evaluate physiotherapists’ satisfaction with using the wearable device in rehabilitation. Method: Patients with hip fracture that require rehabilitation at home will be invited to participate and randomly assigned to one intervention arm. The primary outcome is balance, measured by postural sway using an Inertial Measurement Unit and by Functional Balance test for Geriatric patients. Secondary outcomes are functional independence in everyday activities, measured with the Barthel Index, and health-related quality of life measured with EuroQol 5 Dimension questionnaire and EuroQol Visual Analogue Scale for health and user satisfaction measured by the User Satisfaction Evaluation Questionnaire. Discussion: This study protocol is the first step in securing the research process before performing a full randomized controlled trial. The next step will be a pilot- and feasibility study.

## 1. Introduction

Even if the incidence of hip fractures is no longer increasing in the Western world, fracture care and rehabilitation will still be a future challenge for the healthcare system [1] due to longer life expectancy, and thereby more individuals will be at risk for hip fracture [2,3]. Many of the risk factors associated with sustaining a hip fracture, such as age, previous fractures, inactive lifestyle, dementia, neuromuscular dysfunction, and malnutrition [4], will also interfere with rehabilitation and thus call for specialized efforts [5]. In addition, the trauma and surgery following a hip fracture can trigger deterioration in terms of delirium, depression, and infections [6,7]. Reduced balance and fear of falling both cause and follow a fracture and need to be addressed in rehabilitation [8]. The risk of new fractures is particularly high immediately after a fracture, which calls for interventions to prevent future fractures [9]. Additionally, the patient’s perception of the rehabilitation process is important for reaching the goals [10]. There is a lack of randomized controlled trials (RCT’s) studying the effects of rehabilitation after a hip fracture [11]. Additionally, the need for using novel methods when evaluating the effect of rehabilitation, such as data captured with wearable devices, has been acknowledged [12]. Examples of such data are the number of steps per day, gait flexibility, and balance [13,14,15]. The use of modern technology might benefit in this [15].

The use of tailored intervention protocols towards patients’ needs and capabilities is recommended, with a focus on balance and proprioceptive endurance together with physical and mental independence [16]. A patient-centered intervention is needed, as individuals with a hip fracture will differ in many aspects, such as pre-fracture medical history and activity, type of surgery, and capability to recover [5,16]. The High-Intensity Functional Exercise (HIFE) program was developed specifically for frail older patients with hip fracture [17], aiming at improving muscle strength, balance, gait, and mobility [18]. HIFE is a person-centered intervention protocol, with exercises chosen for each individual after assessment by a physiotherapist. The program is regularly adapted during the rehabilitation period. HIFE has been evaluated among persons with dementia [19] and among persons living in nursing homes [20], but has to our knowledge not been evaluated when applied to rehabilitation in community health care.

RCT’s studying the effect of rehabilitation after hip fracture are few [11], and their external validity has been questioned as they are performed within a strict protocol [21]. Hence, RCT’s applying tailored intervention protocols, such as HIFE, might increase the usefulness of results from such an RCT in clinical practice.

To evaluate the effectiveness and reliability of rehabilitation programs, a variety of tests and scales has been used in the past, such as Functional Balance for Geriatric Patients (FBG) [22,23] and the Romberg test [24]. Increased postural sway is an important fall risk and can therefore be of interest when assessing effect of rehabilitation after hip fracture [25]. Postural sway can be measured in the individual’s home with wearable devices, a measurement that until now demanded a laboratory environment [13]. However, other outcomes can be of importance for evaluating the effect of rehabilitation programs. Walking speed has a relation to fall risk as well as mortality [26,27], step length has a relation to fall risk [26], and physical activity has a very strong relation to overall health [28]. Wearable devices can monitor physical activity, gait, and position of the body 24 h per day and also provide specific information regarding step length and walking speed [15]. Therefore, they are suitable for individualizing treatment programs [12]. Finally, wearable devices will render feedback to the physiotherapist, in terms of body positions and movements, and help the physiotherapist to adjust intensity and content of the rehabilitation program. We believe this will increase the external validity of the planned RCT’s, better mimicking a real-world setting.

We present a study protocol of an RCT with three intervention arms. The aim of the trial is to investigate if there are any differences in outcomes of rehabilitation after hip fracture between different rehabilitation interventions according to (1) HIFE, (2) HIFE with the addition of continuous measures of movement and body positions with a wearable device, or (3) standard rehabilitation in community healthcare. A secondary aim is to evaluate how satisfied physiotherapists are with using the wearable device in the rehabilitation process and if there are any differences between the three interventions in respect of the amount of home visits or telephone calls by the physiotherapist.

Our hypothesis is that HIFE and continuous measures of movement and body positions with a wearable device will have positive effects on balance, functional independence in everyday activities, and health-related quality of life compared with standard rehabilitation or HIFE without continuous measures. We also hypothesize that continuously measuring movements and body positions will support the physiotherapist in planning further contact with the person and that user satisfaction (the physiotherapist) will be high.

## 2. Materials and Methods

This is a study protocol of an RCT with three arms: two interventions and one control.

### 2.1. Setting

The study will be performed in Malmö, which is the third-largest city in Sweden, with about 330,000 inhabitants. In Malmö, about 700 persons are treated for hip fractures every year. We estimate that about 25% of these will fulfill the inclusion criteria for this study and that it therefore will take about 12 months to allocate the 144 participants needed.

### 2.2. Recruitment and Inclusion/Exclusion

Inclusion criteria will be patients at any age who are discharged from hospital after treatment for a hip fracture, living in Malmö, and who are unable to visit a rehabilitation facility and therefore request treatment at home. Another inclusion criterion is the ability to read and understand the Swedish language or the ability to understand information through an interpreter. Since major neurological diseases that have an impact on balance and walking ability will affect the possibility to perform exercises in the HIFE program, the presence of such a disease is an exclusion criterion. Since we expect that persons with a diagnosed cognitive disease, or moderate to severe cognitive impairment will need more assistance from caretakers to perform the HIFE program and to use the wearable device than the project has possibility to provide, this is also an exclusion criterion and will be assessed by a physiotherapist (PT).

Persons fulfilling the inclusion-criteria will be informed about the study at the first home visit by the PT. Those who accept to participate provide their written consent and a second home visit is scheduled.

### 2.3. Instrumentation

An Inertial Measurement Unit (IMU) measures linear accelerations and rotational velocities, often combined with a GPS to reduce the drift in the position level [28,29]. Two different IMU’s will be used in the study: one for measuring postural sway and one for measuring body positions and movements. An IMU containing algorithms for measuring postural sway will be used in all three intervention arms and obtain measures of postural sway in the anterior-posterior and medio-lateral direction at baseline and at follow ups. The IMU used has shown good validity and reliability for measuring postural sway [13]. When measuring postural sway, the IMU is attached to the lower back and postural sway is measured when the participant is standing still, for 30 s. Another IMU, containing algorithms for measuring body positions and movements will be used in one of the intervention arms (intervention B). Body positions are time spent sitting, time spent standing or walking, time spent in supine, prone, and side lying. Movements measured are strides, step time, falls, near falls, and variation in gait. The algorithms in this IMU were developed within the Modern Technology against Falls (MoTFall) project and have shown good sensitivity and specificity for measuring a near fall [15]. When used in the intervention, the participant wears the IMU on the right thigh, approximately 10 cm above the knee, under the clothes, attached with skin-friendly adhesives. The IMU is worn 24 h per day and is charged twice a week. Data from the IMU is sent through a router mounted in the participant’s home, to a platform, where the PT can obtain the data simultaneously and follow the participant’s progress in the rehabilitation process. Data collected during time when the participant is too far away from the router is saved in the IMU and uploaded to the platform when the IMU is charged.

### 2.4. Interventions

In order to increase the usefulness of the results from this RCT, all three groups receive interventions that are tailored to each participant, after assessment by a PT, either within the specified frame of standard rehabilitation (control group) or HIFE (intervention A and B). Additionally, the rehabilitation time periods are tailored to each participant in order to adjust the study to a clinical setting. However, a minimum number of sessions as well as a time interval for the rehabilitation period will be defined after analysis of the results collected in the planned pilot and feasibility study.

Control group: the intervention comprises the standard rehabilitation services: walking training and adaptions to the walking pattern of the patient prior to surgery together with functional exercises [30]. The intervention is tailored to each patient, based on the type of fracture, type of surgery, and assessment by the PT as well as treatment goals.

Intervention A: the intervention comprises the HIFE protocol and, if necessary, other additional exercises. HIFE consists of five exercise categories depending on the capabilities of the patient. A task of walking a short distance (5–10) meters without aid works as a guideline for the PT to select the most suitable exercises for each individual. The five exercise categories and exercises included in each category are shown in Table 1. The PT selects the timetable of the session and creates a progressive high-intensity program based on the pace of the patient. There are three intensity scales for both strength exercises, which depend on the sets of Repetition Maximum (RM) and the balance exercises where postural stability may be challenged close to the limit of maintaining postural stability (Table 2). A 5-min warmup of lower and upper limbs is applied while sitting before the balance exercises begin. Patients start the warmup with walking on the spot, opposing arm swings at the side of the body, “sewing-machine” steps, “picking apples” movement towards different directions, knee stretches, and steps to the side and back of both legs alternately. The equipment needed for the sessions is portable and consists of step boards and chair cushions (5 cm height min), weighted belts (1 kg), soft pads, mattresses and balls, bean bags, belts with handles, and chairs without arm support. All categories have various exercises for the PT to select (Table 1). Difficulty can be increased by providing less assistance or use softer surfaces. Strength intensity is enhanced with weight belt on A and D categories [18]. HIFE has been shown to improve balance, gait, and muscle strength among older persons who were dependent in activities of daily life [31].

Intervention B: the intervention comprises the HIFE rehabilitation protocol, and, if found necessary by the treating PT, other additional exercises. In addition, follow-up and feedback during the rehabilitation period will be given via an IMU, which participants wear 24 h per day until the rehabilitation period has ended (i.e., treatment goals are achieved). The treating PT is thereby provided with specific information regarding time spent per day in sitting, lying, and standing, the total amount of steps per day, any changes in walking speed, etc. Hence, follow-up and feedback can therefore include specific information from the PT to the patient regarding the progress of rehabilitation.

### 2.5. Outcomes

The primary outcome is balance in terms of postural sway and functional balance. Measures of postural sway are performed with the patient standing with heels approximately 10 cm apart and feet pointing about 30° outwards for 30 s with eyes open (EO) and then 30 s with eyes closed (EC). During the measure, an IMU is mounted on the patient’s lower back, in level with L5. The IMU has shown good validity and reliability for measuring postural sway compared to the golden standard (force plate) [13]. Functional balance is assessed with the Functional Balance test for Geriatric patients (FBG), and grades the performance with points, where 0 stands for no execution and 6 for the higher level of performance. FBG evaluates the ability of the patient to sit and stand up, maintain a standing position, walk, and turn. The test includes four activities that the patient shall complete, and every activity has 7 levels of difficulty, indicating the level of independence in each task. The maximum points achievable is 24 [32]. The FBG has shown good validity and reliability when compared to the golden standard (Berg Balance Scale) [22].

Secondary outcome measures are functional independence in everyday activities, health-related quality of life, and the physiotherapist’s satisfaction with the IMU.

Functional independence in everyday activities will be assessed using The Barthel Activity of Daily Living questionnaire. Participants are asked how they manage various everyday activities such as food intake, locomotion, toilet visits, dressing, bathing, transferring, and continence. Ten activities are included, rated on a three-graded scale 0–2 with 0 indicating the worst condition/state and 2 the best condition/state. The maximum score is 20 [33].

Health-related quality of life will be measured by the EuroQol 5-Dimension Questionnaire (EQ5D). EQ5D is a generic instrument to measure mobility, self-care, everyday activities, pain, and anxiety, with five response alternatives, ranging from no problem to unable/extreme [34]. The EQ5D also consists of a visual analog scale, where the participant is asked to rate their health on a vertical scale, where 100 is the best imaginable health state, and 0 is the worst imaginable health state. EQ5D is widely used for monitoring health status among different patient groups all over the world [35].

User satisfaction will be assessed with the questionnaire User Satisfaction Evaluation Questionnaire (USEQ). USEQ consists of six questions where users fill in how satisfied they are with using a system in rehabilitation on a score from 1 (not at all) to 5 (very much). Since it is PTs who fill in the questionnaire by the end of intervention B in this study, the sentence “in your work” was added to the questions as well as “information from the system” instead of only “the system”. The total score lies from 6 (min) to 30 (max). To compute the score, all questions are considered positive except Q5, which is a negative question. Thus, if the person selects 3 in Q1, we add 3 to the total score; on the other hand, for Q5 we subtract the numerical value of the response from 6, and if a person selects 2 in Q5 4 is added to the total value [36].

Information about the number of home visits and telephone calls necessary for the patients to acquire independence is generated through medical records.

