### 2.6. Procedure

Background data on age, sex, method of surgery for the hip fracture, and medication will be collected at baseline. All other measures will be collected at baseline and end of the rehabilitation period. Postural sway and balance will also be assessed 3 months after the end of the rehabilitation period. At the end of the rehabilitation period, physiotherapists fill in USEQ and also record how many home visits were performed and time spent at each home visit as well as the number of phone-calls each participant required.

Baseline data, including information about age, sex, method of surgery for the hip fracture, and medication, as well as outcome measures, will be obtained by a PT at a regular home visit. Follow-up measures will be performed at the end of the rehabilitation period, including primary and secondary outcome measures. The rehabilitation period is defined by the needs of the individual participant and can hence differ in time between participants.

At the end of the intervention treatment, the PTs will fill in the USEQ questionnaire regarding how satisfied they were with using the information from the IMU. During the study, PTs will document the duration and number of home visits as well as telephone calls. PTs time and number of visits is not a pre-designed factor, and it will adapt to the patient’s necessities. The treating PT will also take notes regarding participants who discontinue or deviate from the intervention’s protocols, including reasons for discontinuing or deviating.

All PTs in community healthcare in Malmö, who rehabilitate persons with hip fracture in the Malmö municipality, have received education in the HIFE program. Additionally, workshops including an introduction of the IMU, how to use it, and how to retrieve data from it have been performed. Inclusion of participants to the pilot and feasibility study started in May 2021 and is expected to be completed in December 2021. After that, any necessary changes to the study protocol will be made and a decision whether the full RCT should be conducted will be made.

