### 2.7. Sample Size

Since balance, measured by postural sway, is the main outcome measure, postural sway was used to determine the statistical power of the study. We used results from a previous study [25] with a mean value of 1.8 mm/s for difference in postural sway in the anterior-posterior (AP) direction between two groups of community-dwelling older persons. Since we want to calculate differences between all three groups, a significance level of 0.017 was determined, giving a necessary sample size of 43 participants in each group to reach a power of 80% [37]. To compensate for dropouts, the sample size was set to 48 participants in each group.

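### The primary outcome is not fixed to one measure and visit: Outcomes makes sway and FBG jointly primary, Sample Size powers on anterior-posterior sway alone, and the 0.017 level covers only the three arm comparisons.

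*Protocol article*

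**What the plan says.** The protocol article describes the primary outcome in two ways.

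- **Both instruments.** The Abstract says: "The primary outcome is balance, measured by postural sway using an Inertial Measurement Unit and by Functional Balance test for Geriatric patients". Section 2.5 (Outcomes) agrees: "The primary outcome is balance in terms of postural sway and functional balance". Neither ranks the two.
- **Sway alone.** Section 2.7 (Sample Size) says: "Since balance, measured by postural sway, is the main outcome measure, postural sway was used to determine the statistical power of the study". The planning difference there is 1.8 mm/s in the AP direction, with no eye condition and no visit. The level of 0.017 is explained only by the wish to compare all three groups.

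The number of available measures comes from other sections.

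- Section 2.3 (Instrumentation): the sway device will "obtain measures of postural sway in the anterior-posterior and medio-lateral direction at baseline and at follow ups".
- Section 2.5: each sway test is done with eyes open and then with eyes closed. FBG gives one total score: "The maximum points achievable is 24".
- Section 2.6 (Procedure): after listing the background data, it says "All other measures will be collected at baseline and end of the rehabilitation period", and then "Postural sway and balance will also be assessed 3 months after the end of the rehabilitation period". The same section also says that the follow-up at the end of rehabilitation includes the primary and secondary outcomes.

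Section 2.9 (Statistics) gives ANOVA or Kruskal-Wallis followed by a post-hoc analysis. It has no rule across measures or visits.

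**The concern.** A reader cannot tell from the article which result decides the trial. Sway is measured standing still, whereas FBG covers sitting, standing, walking and turning. The two could disagree, and nothing says which prevails or whether both are needed.

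The level of 0.017 is a correction for three pairs of arms on one measure at one visit. If the primary claim can rest on several measures or on either visit, that correction no longer holds the error for the claim as a whole.

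The visit matters for a second reason. Section 2.8 foresees an assessor unaware of allocation only for the 3-month follow-up, once pandemic restrictions are lifted. Leaving the visit open also leaves open whether the main result rests on blinded or unblinded assessment.

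**Working it through.** **1. Reproduce the plan's level.** 0.05 / 3 = 0.01667, which rounds to 0.017. It matches three pairwise comparisons and nothing more.

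**2. Reproduce the plan's size.** Section 2.7 gives no SD, so 43 per group can only be solved backwards. From n = 2(z₁₋α/₂ + z₀.₈)² SD² / Δ², with α = 0.017, Δ = 1.8 mm/s and n = 43:

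SD = 1.8 × √(43/2) / (z₁₋α/₂ + z₀.₈) ≈ 2.585 mm/s.

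This returns 43 per group at 80% power, so the size fits one AP sway variable compared over three pairs. Dropout: 43 / 0.90 = 47.8, rounded up to 48.

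**3. Count the measures.** 2 directions × 2 eye conditions = 4 sway measures; + 1 FBG score = 5; × 2 follow-up visits = 10. With 3 pairs each, that is 30 pairwise tests. Ten is the widest reading, so narrower ones are shown too.

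**4. False-positive risk if any significant pair counts.** Simulation with no true difference: three equal arms, equally correlated normal measures, each pair tested two-sided at 0.017, 200,000 to 300,000 replicates. The documents give no correlations, so a range is shown.

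| Reading of the primary outcome | Measures | Corr. 0 | Corr. 0.7 | Corr. 0.9 |
|---|---|---|---|---|
| One measure, one visit | 1 | 4.5% | – | – |
| AP sway, two eye conditions, one visit | 2 | 8.7% | 7.6% | 6.5% |
| AP sway, two eye conditions, two visits | 4 | 16.7% | 12.2% | 8.8% |
| All five measures, one visit | 5 | 20.4% | 14.0% | 9.4% |
| All sway measures, two visits | 8 | 30.7% | 18.2% | 11.3% |
| All measures, two visits | 10 | 36.7% | 20.3% | 12.2% |

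Cross-check for ten independent measures: 1 − (1 − 0.0447)¹⁰ = 0.367.

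Sensitivity for ten measures:

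- Requiring a significant ANOVA at an assumed 0.05 first changes little: 35.3% at correlation 0 and 19.5% at 0.7.
- Unequal assumed correlations (sway with sway 0.4 to 0.8, sway with FBG 0.2 to 0.4, between visits 0.4 to 0.8) give about 22 to 33%.

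**5. The opposite rule: two measures must both succeed.** For one sway variable and FBG at one visit, P(both) = 2 × P(one) − P(either):

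- correlation 0: 2 × 0.0445 − 0.0868 = 0.002;
- correlation 0.9: 2 × 0.0447 − 0.0651 = 0.024.

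Both lie below 5%. Under this rule the cost is power, not false positives.

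**6. Price of correcting over all 30 tests.** 0.05 / 30 = 0.00167 holds the overall error at about 4.6% for independent measures. At the back-solved SD, 43 per group would then have about 53% power, and 80% would need about 66 per group before dropout.

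**The case against.** The strongest reply is that the article does give some priority. Section 2.7 ranks sway as the main measure and powers on AP sway. Section 2.6 places the primary and secondary outcomes at the end of rehabilitation and adds the 3-month assessment as a further one. The two directions appear in a description of the device, and the eye conditions in a description of the test. Neither text says that each combination is a separate primary endpoint. The Abstract and Section 2.5 join the two instruments with the word and, which could mean that both must succeed. A statistical analysis plan that is not shown may set a hierarchy, and the article allows changes after the pilot.

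Much of this stands. A reader might infer that the trial's false-positive rate simply is 20 to 36%, or that no measure or visit has any priority. The documents support neither. The first needs ten co-equal measures, correlations no higher than 0.7 and a rule that any single significant result suffices; the article states none of these. The second overlooks Sections 2.6 and 2.7.

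What does not stand is that the matter can be left to an analysis plan. The Abstract and Section 2.5 rank the primary outcome differently from Section 2.7, and that conflict lies in the text shown. Section 2.6 suggests a main visit but does not fix one. Even the narrow reading of AP sway at one visit leaves two eye conditions.

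**Conclusion.** The point holds. The primary outcome is defined in two incompatible ways, and the stated level matches only one measure at one visit. As written, the primary claim has no single deciding test and no error control across measures or visits.

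The size is conditional. If any significant pair counts, every reading with more than one measure in the table exceeds 5%, from 6.5% (AP sway in two eye conditions at one visit, correlation 0.9) to 36.7% (ten independent measures). The upper end assumes independence, which is implausible for repeated sway measurements on the same person. If both sway and FBG had to succeed, the error would not be inflated this way.

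Confidence is high in the inconsistency and in the mismatch between 0.017 and the outcome as defined. It is low in any single percentage.

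**What to change.** Reconcile the Abstract, Section 2.5 and Section 2.7 before the full trial starts.

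- **Name one primary variable at one visit.** AP sway is the natural choice because it is the powered measure. State one eye condition, matching the one behind the 1.8 mm/s; the sponsor can take this from the cited study, which is not available here. State whether the visit is the end of rehabilitation or 3 months later. Then 0.017 and 43 per group belong to the test that decides the trial.
- **Make the rest secondary:** medio-lateral sway, the other eye condition and the other visit.
- **Settle FBG.** Make it secondary, or test it in fixed order after sway. If it stays co-primary, state whether one or both must succeed, set the level to match, and restate the power, since no FBG effect is given.

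The cost is a wording amendment, which fits the protocol revision already foreseen after the pilot. Unless FBG stays co-primary, no participants are added. The downside is that FBG, the other sway measures and the second visit lose equal primary status.
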